**FIGURE 1 F1:**
[figure not shown]
Flowchart of the protocol.

### 2.3. Study population

According to national guidelines (Socialstyrelsen, 2018), schizophrenia includes positive and negative symptoms. The criteria provided in the current guidelines (Socialstyrelsen, 2018) and described in section “2.3.1. Inclusion criteria” is applied during the study inclusion at the beginning of the study. The study population (*N* = 60) includes adults diagnosed with schizophrenia or schizophrenia-like disorders according to the criteria presented below.

#### 2.3.1. Inclusion criteria

People aged 18–65 years with schizophrenia diagnosis or schizophrenia-like disorders, performing moderate to vigorous physical activity less than 150 min/week based on self-report, are included in the study. Outpatients with schizophrenia (F20), schizoaffective disorder (F25), and acute schizophrenia-like psychotic disorder (F23.2) with at least mild symptom severity (>21 on 7 negative items of PANSS) will be included.

#### 2.3.2. Exclusion criteria

People with current or recent history of substance abuse, bipolar disorder, severe autism, suicidal, severe physical illness, inability to read and understand the Swedish language, inability to participate in a group setting or patients who reported more than 150 min of physical activity at moderate to high level per week are excluded from the study. Patients with less than 21-point score on PANSS negative scale will be excluded.

### 2.4. Recruitment

Recruitment is planned to take place at an outpatient psychiatry center, where clinicians, such as psychiatrists, nurses, occupational therapists, social workers, physical therapists and assistants are asked to inform patients about the study and recruit them during their regular check-ups. Written and informed consent will be obtained from all participants. After written consent is received, the diagnosis according to the inclusion criteria will be verified in the medical records or by examination by a psychiatrist.

Schizophrenia patients and their legal guardians, who consent to the study and are eligible for the study according to the inclusion criteria, will be offered to proceed with the baseline measurement.

### 2.5. Modes of delivery

The intervention covers various themes through three different parts (4 weeks per part) with the aim to improve clinical symptoms, physical fitness, cognitive skills and emotion regulations. The intervention was developed by a team consisting of a neuroscientist, a psychiatrist, dance teachers and physiotherapists with previous experience in designing dance and movement interventions for different target groups with internalizing problems (Duberg et al., 2013), functional abdominal pain (Högström et al., 2022) and profound intellectual and multiple disabilities (Lundqvist et al., 2022). The intervention is further described in Table 1. The exercise is partly accompanied by instrumental music and recorded nature sounds and partly made in silence paying attention to one’s own bodily rhythm. The exercise consists of tasks related to cardio and strength training, balance, conscious breathing, body awareness, mental imagery (nature visualizations), flexibility, emotional expression, and movement anticipation together with the facilitator and fellow participants. All the tasks are practiced during a flow of 60-min exercise without any major breaks. To meet the needs of the participants in the group, adjustments and modifications will be presented when necessary. Complexity and physical intensity of the tasks will gradually increase over the 12 weeks intervention periods.

**TABLE 1 T1:** Content of the biweekly 12-week intervention on mixed exercise program with creative movement for adults with schizophrenia.

Minutes	Section	Description	Purpose
		Gathering in a circle	Establishing a feeling of being included
2–4	Body scan	Scanning through the body parts Part 1 (moving), Part 2 (self-massaging and tapping), and Part 3 (moving)	Body awareness Hedlund and Gyllensten, 2010; Ferri et al., 2012; Martin et al., 2016; Gökcen et al., 2020
3–7	Gentle movement, flexibility (warm up/preparation)	Stretching arms, sides, neck, rotating shoulders, back, hip, and knees	Body awareness, increased blood-circulation and synovial fluid, stimulate mental presence. Hedlund and Gyllensten, 2010; Ferri et al., 2012; Martin et al., 2016; Bryl et al., 2020
8–10	Cardio	Reaching, jumping, walking, running	Strengthen cardio-vascular function. Soundy et al., 2014; Firth et al., 2015; Vancampfort et al., 2015b; Cheng et al., 2017
8–10	Choreography	Memorizing a dance sequence	Enjoyment, coordination, body awareness Firth et al., 2017a,b; Chen et al., 2018
7–9	Strength	Strength training for large muscle groups: legs, arms, back, core	Increase strength in large muscle groups. Martin et al., 2017
5–8	Balance	Walking carefully with one-leg-balances	Improve balance through increased proprioception and interoception. Hedlund and Gyllensten, 2010; Fuchs, 2018
4–6	Mirroring	Moving in synchrony with a partner/in a small group	Social interaction Hedlund and Gyllensten, 2010; Röhricht et al., 2011; Ebisch et al., 2014; Bryl et al., 2020; Gökcen et al., 2020; Bryl and Biondo, 2021
4	Emotional expression	Expressing with the face and body basic positive emotions: joy, tenderness, curiosity, gratefulness	Emotional expression Röhricht et al., 2011; Ebisch et al., 2014; Lee et al., 2015; Bryl and Biondo, 2021
4	Improvisation	Own improvisation with the guidance of the facilitator	Röhricht et al., 2011; Bryl et al., 2020
2–4	Body scan	Scanning the body and grounding back to the current moment	Body awareness Hedlund and Gyllensten, 2010; Ferri et al., 2012; Martin et al., 2016
Total duration: 60 min			

### 2.6. Randomization

The participants will be randomly divided into two groups, 30 patients who will receive the mixed exercise program with creative movement intervention in addition to continuing their conventional treatment plan and 30 patients who will only receive their usual treatment. Randomization in the main RCT study will be carried out in sealed envelopes after the baseline measurements. An external statistician will prepare the envelopes that will be delivered to the participants by the research team. Thus, the randomization will be blinded to the research team, meaning the research team will not know the group or identify of the participants when analyzing the data. Due to the nature of intervention studies, blinding toward the participants is not possible. Physical activity cannot be blinded, meaning that the patients know whether they are receiving the treatment or not.

### 2.7. Sample size

The sample size is calculated according to the primary outcome PANSS. For the primary outcome (improved negative symptoms according to PANSS after 12 weeks), the total number of required study participants was calculated (Curcic et al., 2017). Calculation was based on a minimum improvement of 15% on total PANSS score between the intervention and control group. With a power of 80% and a significance level of 0.05, we calculated the sample size to be *N* = 60 (30 intervention + 30 control participants), including a 25% dropout rate.

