**Methods:**

The study is a mixed-method randomized controlled trial to evaluate the effects of a 12-week intervention for adults with schizophrenia. The treatment group (30 participants) will receive the intervention in addition to standard care and the control group (30 participants) only standard care. The intervention consists of 24 biweekly sessions with a duration of 60 min. The pre-test (weeks from 4 to 2 prior to the intervention) and post-test (week 12) include clinical measure (PANSS), quality of life, social performance, movement quantity, brain function and eye tracking measures. In addition, a treatment subgroup of 12–15 participants and their family member or other next of kin will complete a qualitative interview as a part of their post-test. Two follow-up tests, including clinical, quality of life, brain function and eye tracking will be made at 6 and 12 months from the completion of the intervention to both study groups. The primary outcome is change in negative symptoms. Secondary outcome measures include general and positive symptoms, quality of life, social performance, movement quantity, brain function and eye tracking. Explorative outcome includes patient and family member or other next of kin interview.

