### 1.5. Aims and expected results

The primary aim of the study is to investigate the effects of mixed exercise program with creative movement and cognitive, emotional and social stimulation as add-on to ongoing pharmacological treatment, in treating negative symptoms of schizophrenia. Previous studies with dance movement therapy, body psychotherapy or physical exercise show reduction in negative symptoms of schizophrenia (Röhricht et al., 2011; Lee et al., 2015; Martin et al., 2016; Gökcen et al., 2020), and that the change in these symptoms can be measured with PANSS (Röhricht et al., 2011; Lee et al., 2015; Sabe et al., 2020; but see but see also Bryl et al., 2020 for qualitative but not significant quantitative results). Thus, our hypothesis is that the intervention will improve negative symptoms detectable with PANSS in comparison to the control group. The reduction is anticipated to correlate with changes in brain function and physical measures. In line with previous studies (e.g., Röhricht et al., 2011; Lee et al., 2015; Curcic et al., 2017; Sabe et al., 2020), we will measure both negative and positive symptoms as well as general psychopathology, i.e., total PANSS score and look separately at the three symptom classes.

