**Primary outcome measure**							
PANSS negative symptoms subscale	V, O two items			V, O two items		V, O two items	V, O two items

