**Secondary outcome measures**							
General PANSS and positive symptoms subscale (45 min)	V, O two items			V, O two items		V, O two items	V, O two items
CGI-S and CGI-I (5 min)	V			V, O for CGI-I		V, O for CGI-I	V, O for CGI-I
CDSS (10 min)	V			V		V	V
PSP (10 min)	V			V		V	V
Burden of care, VAS (5 min)	O			O		O	O
BAQ-sv, 10 min	X			X		X	X
EQ-5D-5L, 5 min	X			X		X	X
Weight, length, BMI, 5 min	X			X		X	X
Waistline, 1 min	X			X		X	X
Blood pressure, 10 min rest, 2 min test	X			X		X	X
Resting pulse, 1 min	X			X		X	X
Breathing frequency, 1 min	X			X		X	X
Postural stability/balance, 10 min	X			X		X	X
Chair stand test, 3 min	X			X		X	X
fNIRS-EEG combined with eye tracking during cognitive paradigms including STROOP, verbal fluency, AX-continuous performance test, Emotion regulation test. 45 min	X					X	X
Everyday activity/accelerometer	X (measured at home, 7 days)					X (measured at home, 7 days)	
Motion Capture 60 min		X	X		X		

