The challenge in a holistic intervention combining physical, creative and social components is that we cannot know which individual components contribute to the changed clinical and health outcomes. The influential subcomponents in a positive outcome could be the supportive group setting, instructors, music, or specific parts of movement exercises. However, we hypothesize that the core of the intervention is the *combination* of all these subcomponents together. Methodologically, we follow the highest standards for clinical studies including the randomized controlled design, one-year follow-up and the combination of quantitative and qualitative measures related to clinical symptoms, physical abilities, and cognitive, emotional and cerebral functions.

Several aspects of our trial design are worth noting as potential limitations. Since the sample size is calculated according to the primary outcome PANSS, the results of the secondary outcomes should be considered cautiously, and the results replicated in future studies. If the sample size was calculated according to the amount of all the measurements, the sample size would be so high that it would be beyond realistic possibilities, and this study would very likely never be completed. Some of the measures, such as PANSS, are subjective whereas other measures, such as brain imaging, are objective. Although it is difficult to blind the assessor during the assessment of the objective measures, the person performing the analysis will be blinded. Since this is the first time we use such intervention of creative physical exercise, we cannot know whether the design will be robust enough to capture changes with the content (e.g., physical activity increasing heartrate, social interaction, body awareness) and dosage we defined (twice a week for 60 min per session). However, the content and dosage are based on previous literature on creative movement interventions in schizophrenia (Martin et al., 2016; Cheng et al., 2017; Bryl et al., 2020).

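### The sample size is stated for negative symptoms but calculated on total PANSS, so the 80% power is not established for the primary endpoint

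*Protocol article*

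**What the plan says.** The primary outcome is named consistently. The abstract states: "The primary outcome is change in negative symptoms". Table 2 lists "PANSS negative symptoms subscale" as the only primary measure, and section 3.1.1 repeats it. Table 2 places "General PANSS and positive symptoms subscale" among the secondary outcomes. Section 1.5 plans to measure "total PANSS score and look separately at the three symptom classes", so the article itself treats the total and its components as different measures.

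Section 2.7 opens on the right endpoint: "For the primary outcome (improved negative symptoms according to PANSS after 12 weeks), the total number of required study participants was calculated". The next sentence changes the score: "Calculation was based on a minimum improvement of 15% on total PANSS score between the intervention and control group". It continues: "With a power of 80% and a significance level of 0.05, we calculated the sample size to be" 60, that is 30 per arm, with 25% dropout included. The Discussion (section 7) relies on this calculation: "Since the sample size is calculated according to the primary outcome PANSS, the results of the secondary outcomes should be considered cautiously".

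**The concern.** Within one paragraph the calculation is attributed to negative symptoms and then based on total PANSS. A power figure belongs to one variable, with its own expected difference and its own SD. A 15% difference on the total does not translate into a known difference on the seven negative items: the total also contains the positive and general items, and its mean and spread differ. Entry is also restricted on the negative subscale (above 21, section 2.3.1), which acts directly on the mean and spread of that subscale and only indirectly on the total.

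What is at stake is how the primary result is read. If the comparison on negative symptoms is not significant, readers will take it as the result of a trial with 80% power for that endpoint. The Discussion also uses the calculation to set the primary result apart from the secondary ones. Nothing in the article gives an effect, an SD or a power for the negative subscale.

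**Working it through.** **Inputs from the article.** N = 60, 1:1 allocation, 25% dropout, 80% power and significance level 0.05 (section 2.7); two-tailed tests (section 3.3.3); entry above 21 on the negative subscale (section 2.3.1), so the baseline mean should not lie below about 22.

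**Assumptions, because the article gives no figure.** A continuous outcome compared by a two-sample t-test; baseline mean on the negative subscale of 22 to 28; SD of 4 to 7; for adjusted analyses, a baseline to week-12 correlation r of 0.5 to 0.6.

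**1. Can N = 60 be reproduced?** No. The article gives no SD, no mean total PANSS and no standardized effect. The calculation can only be run backwards.

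Evaluable patients: 60 × (1 − 0.25) = 45, or 22.5 per arm.

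Standardized difference d with 80% power, normal approximation: d = (1.960 + 0.842) × √(2/22.5) = 0.835. With the noncentral t distribution: d = 0.855.

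**2. What this means for total PANSS.** A 15% difference equals 0.855 SD only for particular pairs of mean and SD: mean 80, 12.0/0.855 = SD 14.0; mean 90, 13.5/0.855 = SD 15.8; mean 100, 15.0/0.855 = SD 17.5. N = 60 could therefore be a sound calculation for total PANSS, but none of these pairs is in the article and none concerns the primary endpoint.

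**3. The same 15% applied to the negative subscale.** Difference = 0.15 × mean; d = difference/SD; power from the noncentral t with 22.5 per arm, unadjusted:

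| Assumed mean | 15% in points | SD 4 | SD 5 | SD 6 | SD 7 |
|---|---|---|---|---|---|
| 22 | 3.30 | 77% | 58% | 44% | 34% |
| 25 | 3.75 | 87% | 69% | 54% | 42% |
| 28 | 4.20 | 93% | 79% | 63% | 50% |

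Unadjusted power reaches 80% only if the SD is no larger than 3.30/0.855 = 3.9 (mean 22), 3.75/0.855 = 4.4 (mean 25) or 4.20/0.855 = 4.9 (mean 28).

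**4. With baseline adjustment.** The residual SD is SD × √(1 − r²). The detectable difference becomes 0.855 × √(1 − 0.25) = 0.74 SD at r = 0.5 and 0.855 × √(1 − 0.36) = 0.68 SD at r = 0.6. At mean 25 and SD 5, power rises from 69% to 81% (r = 0.5) or 87% (r = 0.6). At mean 25 and SD 6 it rises from 54% to 66% or 73%.

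The same 45 patients thus give power well below or well above 80%, depending on a mean, an SD and a correlation that the article does not state for this endpoint.

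**The case against.** **Total may be a slip for negative.** The preceding sentence does name negative symptoms. Nothing in the article confirms a slip, however, and section 1.5 shows that its authors distinguish the total from the subscales. The sentence needs correcting on either reading.

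**The continuous reading is an interpretation.** Section 2.7 names no test, and section 3.3.3 mentions a Fisher exact test and logistic regression for the primary outcome, so 15% could be a responder cut-off. The reference to an improvement between the two groups favours a difference in means, but does not settle it. This objection stands as far as the numbers go: the SD-based figures are conditional on a continuous outcome. It does not touch the mismatch of scores. For the same reason I draw no conclusion about the power of the Fisher test; the test behind N = 60 is not stated.

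**An article may leave the SD and its source to a fuller document.** Agreed. Their absence is not the point; it only prevents reproduction of N. The point is that the effect the article does state is on a score that is not the primary outcome.

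**A reader might infer that the trial is underpowered.** The documents do not support that. Showing only SDs of 5 and above, unadjusted, would put every figure below 80%, but an SD of 4 gives 77% to 93%, and baseline adjustment passes 80% at mean 25 and SD 5.

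**A reader might infer that the Discussion needs its own correction.** It refers only to the primary outcome PANSS, which is ambiguous between total and subscale and becomes accurate once section 2.7 is reconciled.

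**Conclusion.** The point holds as an internal contradiction in section 2.7. The sample size is attributed to the negative subscale but rests on total PANSS, and no other part of the article resolves this. It is not a demonstrated arithmetic error, because N = 60 cannot be recomputed from what is given. The 80% power is not established for the primary endpoint, and its true value could lie on either side of 80%.

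As to size, under a continuous outcome and a two-sided t-test the design detects about 0.85 SD unadjusted, or 0.68 to 0.74 SD adjusted, with 80% power. Carrying the 15% over to the subscale gives about 34% to 93% unadjusted across the assumed means and SDs. These ranges show how open the question is; they do not estimate the trial's actual power. The correction should be made because the power statement governs how a null primary result will be interpreted.

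**What to change.** Keep N = 60 and change section 2.7 in one of three ways:

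- Restate the calculation on the PANSS negative subscale: the assumed between-group difference at week 12, the assumed SD, the test it refers to, and the power that 45 evaluable patients deliver.
- If no credible SD for the subscale is available, replace the 80% claim with the standardized difference detectable with 80% power: about 0.85 SD unadjusted, or 0.68 to 0.74 SD with baseline adjustment at a correlation of 0.5 to 0.6, with the correlation labelled as an assumption.
- If total was written in error and the 15% was meant for the negative subscale, correct the wording.

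The cost is a few sentences, with no extra patients and no change to trial conduct. The drawback is that the restated power may look less favourable than 80%.

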### 2.8. Intervention

The intervention is called “InMotion” to highlight physical activity as a natural part of positive lifestyle habits for adults with schizophrenia. Essential elements of the intervention will include a focus on physical exercise, enjoyment, socialization, and playful creativity in a safe environment. Physical activity is central in the intervention since previous result showed decreased BMI and increased condition (Martinsen and Taube, 2008; Cheng et al., 2017; Girdler et al., 2019), increased memory and social and problem-solving ability (Girdler et al., 2019). Body awareness training is combined with creative movement because of experiences from earlier studies on dance-movement therapy, movement therapy and dance, which have shown decreased schizophrenia-symptoms and increased ability to cope with remaining symptoms (Ren and Xia, 2013; Martin et al., 2016; Koch et al., 2019). When there are challenges with verbal language, social interventions that includes body, senses and action is particularly effective and studies have shown that structured, joyful movement led by instructor is important for people with schizophrenia (Martinsen and Taube, 2008; Kinou et al., 2013; Cheng et al., 2017; Millman et al., 2021). Moving in a group can strengthen the ability to understand one’s own body-language, as well as others. Emotional expression and creativity through movement can increase emotional richness and self-efficacy (Kinou et al., 2013; Millman et al., 2021).

The InMotion intervention shares some similarities with dance movement therapy. Our intervention has similar components especially with the approach by Chace (Bryl and Biondo, 2021). For example, mirroring movement is a core element of the Chacian approach on dance movement therapy (Bryl and Biondo, 2021). However, in our group intervention, mirroring is conducted by a fellow participant instead of the facilitator, whereas in dance movement therapy typically the therapist creates empathic movement reflections in an interaction with the patient (Bryl and Biondo, 2021). In our intervention, the fellow participants do not have a therapist’s education for mirroring a right gesture at the right time, but the mirroring interaction of two participants simulates real-life interactions with an emphasis on the embodied and non-verbal component of such interactions.

The group setting of our intervention is similar to the one used in dance movement therapy for people with schizophrenia (Klingberg and Buchkremer, 2000; Jones et al., 2012; Bryl et al., 2020). In addition, working with and enhancing body awareness, movement and agency for own body and action are some of the core elements of our intervention and dance movement therapy (Bryl and Biondo, 2021). What the InMotion intervention adds to the qualities of dance movement therapy, is the emphasis on physical cardio and strength training (Vancampfort et al., 2015b; Martin et al., 2017; Girdler et al., 2019). A specified amount of time is dedicated to increase the heartrate through fast walking, running, and dynamic movement which engage large muscle groups to achieve moderate to vigorous cardio-training. The intervention also includes strength-training using own body weight such as push-ups, squats and lunges.

